**Methods:**

This study is an open-label, multi-center, parallel, prospective, randomized, interventional clinical study to evaluate the efficacy of CN in combination with CPIs in mRCC patients with International mRCC Database Consortium (IMDC) intermediate- and poor-risk. Synchronous mRCC patients with ≤ 3 IMDC risk features will be randomly allocated to three groups (1, upfront CN; 2, deferred CN; and 3, systemic therapy [ST] only). For ST, the nivolumab plus ipilimumab combination regimen, one of the standard regimens for intermediate- and poor-risk mRCC, is chosen. The primary endpoint is overall survival. The secondary endpoints are progression-free survival, objective response rate, number of participants with treatment-related adverse events, and number of participants with surgical morbidity. We will analyze the genetic mutation profiles of the tumor tissue, circulating tumor DNA, urine tumor DNA, and tumor-infiltrating lymphocytes. The gut and urine microbial communities will be analyzed. The study will begin in 2022 and will enroll 55 patients.

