### Study timeline

After completing the recruitment procedure, clinical and pathological data were collected (Table 1).

**Table 1 Tab1:** Clinical and pathological data

Clinical data				Pathological data
Baseline	Surgery-related	ICI therapy-related	Oncological outcome	
Age	OR note (including any intraoperative events)	Dosage	Overall survival	Pathological TNM staging
Sex	EBL	Cycle	Progression-free survival	Cell type
Height	Surgical morbidity (according to CDC)	Toxicities (graded by CTCAE v5.0)	Objective response rate (according to RECIST v1.1)	ISUP nuclear grade
Weight		Total administration periods		
BMI		Cause of discontinuation		
BSA				
KPS				
IMDC risk feature				
Clinical TNM staging				
Metastatic sites				

*BMI* body mass index, *BSA* body surface area, *CDC* Clavien–Dindo classification, *CTCAE* Common Terminology Criteria for Adverse Events, *EBL* estimated blood loss, *IMDC* International mRCC Database Consortium, *ISUP* International Society of Urologic Pathologists, *KPS* Karnofsky Performance Status, *OR* operating room, *RECIST* Response Evaluation Criteria for Solid Tumors

A flowchart of the study is shown in Fig. 1. Patients will be evaluated for eligibility for surgery. If they are not eligible for surgery, they will start ICI therapy (induction phase). Then, they will be assessed for whether they are eligible for surgery. If not, they will continue with ICI therapy (maintenance phase) (Group C). If they are eligible for surgery, they will be randomly allocated to the deferred CN group (Group B) or ICIs only. If they are eligible for surgery at the first visit, they will be randomly allocated to the upfront CN Group A (group A) or the deferred CN group (Group B). Patients will be randomly allocated in a 1:1 ratio using a computer-generated allocation sequence by a local project nurse. The randomization will be performed on an institutional basis to prevent bias.

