**Fig. 1 Fig1:**
[figure not shown]
Study flowchart. CN, cytoreductive nephrectomy; IMDC, International mRCC Database Consortium; Ipi, ipilimumab; mRCC, metastatic renal cell carcinoma; Nivo, nivolumab; KPS, Karnofsky performance status

Candidates for CN are patients with good performance status (Karnofsky performance status ≥ 80%) and less than three IMDC risk features and whose primary tumor could be surgically removed. Metastasectomy can be performed when the metastatic sites can be surgically removed. All patients eligible for ICI therapy will receive four cycles of intravenous nivolumab (3 mg/kg) plus ipilimumab (1 mg/kg) every 3 weeks as the induction phase, followed by a response evaluation. After the induction phase, intravenous nivolumab (3 mg/kg) will be administered 6 times every 2 weeks as the maintenance phase, followed by response evaluation. Nivolumab monotherapy will be maintained for a maximum of 2 years for those without adverse side effects. During ICI therapy, adverse events will be evaluated once per cycle. Patients will discontinue ICI therapy when they develop serious adverse events, including grade 3 or worse, according to the Common Terminology Criteria for Adverse Events version 5.0 (CTCAE v 5.0). In the upfront CN group, the induction phase will be within 6 weeks of surgery, whereas in the deferred CN group, surgery will be performed within 6 weeks of the induction phase. The study will be conducted over a period of 5 years.

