### Sample size justification

Two prospective RCTs, PROBE (NCT04510597) and NORDICSUN (NCT03977571), are currently ongoing, but do not include an upfront CN arm. We determined the sample size based on the most recent real-world data that analyzed the intermediate/high risk group of mRCC patients stratified into upfront CN, deferred CN, and systemic treatment group [17]. To determine the required sample size for the study, we utilized two calculators for two-group survival analysis [18]. For Calculator 1, with a two-tailed alpha level (*α*) set at 0.05 and a beta level (*β*) of 0.2, along with a proportion of subjects in Group 1 (upfront and deferred CN) of 0.66 and a proportion in Group 0 (ICIs only) of 0.34, the relative hazard was set at 0.37. The calculated number of events needed to achieve 80% power was 35. For Calculator 2, with the total number of events set at 35, and assuming a baseline event rate of 0.53 and a median survival time in Group 0 (ICIs only) of 1.3 years, along with a censoring rate of 0.1 and a planned average length of follow-up of 5 years, the sample sizes required for each group were determined. Therefore, a total of 57 subjects were needed for the study.

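### The survival comparison of nephrectomy with immunotherapy alone, on which the trial is powered, is not randomised under the stated allocation scheme and is confounded by surgical eligibility

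*Protocol article*

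**What the plan says.** The abstract says that patients "will be randomly allocated to three groups (1, upfront CN; 2, deferred CN; and 3, systemic therapy [ST] only". The Primary endpoint section compares overall survival across those three groups. Sample size justification pools A and B and tests them against C, with a "proportion of subjects in Group 1 (upfront and deferred CN) of 0.66 and a proportion in Group 0 (ICIs only) of 0.34". It arrives at 35 events, 57 patients and 80% power for a hazard ratio of 0.37.

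Study timeline gives the working scheme, with three routes:

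- Eligible at the first visit: "If they are eligible for surgery at the first visit, they will be randomly allocated to the upfront CN Group A" or to Group B.
- Ineligible at first, eligible after induction: "If they are eligible for surgery, they will be randomly allocated to the deferred CN group (Group B) or ICIs only".
- Ineligible at both assessments: "If not, they will continue with ICI therapy (maintenance phase) (Group C". No random allocation is described.

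The ratio at each randomisation is 1:1. Surgical candidacy is defined in the text under Fig. 1: "Candidates for CN are patients with good performance status (Karnofsky performance status ≥ 80%) and less than three IMDC risk features", together with a removable primary tumour. Trial entry is wider, from a Karnofsky score of 70 upwards (Inclusion criteria).

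**The concern.** A first-visit-eligible patient can never be in C, and an initially ineligible patient can never be in A. Group B mixes the two populations. The factors that sort patients (performance status, IMDC features, resectability) are partly prognostic, so C is expected to do worse than A, or than A+B pooled, even if nephrectomy does nothing.

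The clocks also differ. Every C patient and every late-entry B patient is allocated only after surviving induction (four 3-weekly cycles, about 3 months). Group A and first-visit B patients are allocated at the start.

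At stake is the primary question. A comparison of patients fit for surgery with a group that includes patients who never were could be reported as randomised superiority evidence.

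**Working it through.** **1. The routes.** Let p be the share eligible at the first visit, and q the share of initially ineligible patients who become eligible after induction. The document gives neither.

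| Route | Share | Allocation |
|---|---|---|
| Eligible at first visit | p | A or B, 1:1 |
| Eligible only after induction | (1−p)q | B or C, 1:1 |
| Eligible at neither | (1−p)(1−q) | C, not randomised |

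Hence A = p/2, B = p/2 + (1−p)q/2 and C = (1−p)(1−q/2). A 1:1 ratio at each step does not by itself give the planned 0.66/0.34 split; that holds only if (1−p)(1−q/2) = 0.34.

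**2. The plan's own figures.** Inputs from Sample size justification: two-sided alpha 0.05, power 0.80, hazard ratio 0.37, split 0.66/0.34, control median 1.3 years, censoring 0.1 (taken as per year), follow-up 5 years.

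- Events (Schoenfeld): (1.960 + 0.842)² / [0.66 × 0.34 × (ln 0.37)²] = 35.4.
- Event probability: λ/(λ+0.1) × [1 − exp(−5(λ+0.1))]. With λ = ln 2/1.3 = 0.533 this is 0.807 in C. With λ = 0.37 × 0.533 = 0.197 it is 0.514 in A+B.
- Weighted: 0.66 × 0.514 + 0.34 × 0.807 = 0.613, and 35/0.613 = 57.1.

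Both 35 and 57 reproduce, but as a two-group calculation that treats the groups as exchangeable.

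**3. How much of the trial randomises surgery against none.** Only the second randomisation does. Holding C at 34%, 1−p = 0.34/(1−q/2). The number randomised is 57(1−p)q. Expected events D are that number × (0.807+0.514)/2. Power at 1:1 is Φ(0.994 × √D/2 − 1.96), where 0.994 = |ln 0.37|. The never-randomised share of C is (1−q)/(1−q/2).

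| q | 1−p | Never-randomised share of C | Randomised B vs C | D | Power |
|---|---|---|---|---|---|
| 0.3 | 0.400 | 82% | 6.8 | 4.5 | 18% |
| 0.5 | 0.453 | 67% | 12.9 | 8.5 | 31% |
| 0.7 | 0.523 | 46% | 20.9 | 13.8 | 45% |

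At the limit q = 1, 57 × 0.68 = 38.8 patients and 25.6 events give about 71%. With C at 34% of 57, this contrast therefore cannot reach 80% whatever q is.

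**4. Illustrative bias with no effect of nephrectomy.** Simulated log-rank test of A+B versus C: 57 patients split as above, first-visit-eligible hazard 0.32 per year, censoring 0.1 per year, 5 years, counting significant results in favour of surgery (about 3–4% when all hazards are equal). The 0.32, the hazard multipliers and q are assumptions.

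| Hazard vs first-visit eligible (late-eligible / never-eligible) | q | Clock from allocation | Clock from enrolment, 3-month induction survival required |
|---|---|---|---|
| 1.25 / 1.25 | 0.3–0.7 | 8–11% | about 5% |
| 1.5 / 2 | 0.3, 0.5, 0.7 | 50%, 39%, 28% | 33%, 26%, 18% |
| 1.5 / 2 | 0.9 | 14% | 10% |

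With 1.5 / 3, clock from allocation and q from 0.3 to 0.7, the range is 45–81%.

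**The case against.** Several points on the other side have weight.

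- **Part of the design is properly randomised.** A versus B among first-visit-eligible patients, and B versus C among those eligible after induction, are sound contrasts. A reader might infer that Group C is wholly non-randomised; the text does not support that.
- **Patients with a Karnofsky score of 70, or over the IMDC limit, are not confined to C.** A reader might infer this from the gap between entry and candidacy criteria. Everyone ineligible at the first visit is reassessed after induction and can reach B if then eligible. What they cannot reach is A.
- **The bias is not all one way.** If survival runs from enrolment, the need to survive induction favours C and partly offsets the fitness difference, as the right-hand column above shows. The article does not say where the clock starts.
- **Adjustment is available in part.** Statistical analysis names multivariate Cox models, and Table 1 collects performance status, IMDC features, stage and metastatic sites. This can reduce confounding but cannot restore randomisation: resectability is not listed, and C contains no first-visit-eligible patient with whom A could be compared.
- **The pooled contrast appears only in the sample size section.** That is true, but the stated power rests on it, and the three-group comparison in Primary endpoint has the same problem for A versus C.

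Fig. 1 is not shown and might qualify the text, but the wording of Study timeline is explicit.

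**Conclusion.** The concern holds as a structural contradiction. The allocation in Study timeline does not produce the three-way randomisation described in the abstract, nor a randomised basis for the pooled comparison that carries the 80% power. A versus C and A+B versus C are confounded by surgical eligibility. This follows from the text and needs no assumed number.

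The power figures of 18–45% assume q between 0.3 and 0.7, C at 34% of 57 and the plan's own event rates. The false-positive rates, from about 5% to 81%, depend on assumed hazards, q and time origin. A reader might take the upper values as an estimate of the error rate; the document supplies nothing to support that, and mild assumptions give rates close to nominal. The direction is towards favouring surgery if ineligible patients survive less well, less any induction-survival offset.

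**What to change.** Reconcile the abstract, Primary endpoint, Study timeline and Sample size justification so that they describe one allocation. If the scheme in Study timeline stands:

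1. Limit randomised claims to A versus B (eligible at the first visit) and B versus C (eligible after induction). Split Group B by entry point and start each survival clock at its own randomisation.
2. Report patients ineligible at both assessments as a separate observational cohort, outside randomised Group C.
3. Label A versus C and pooled A+B versus C as non-randomised, and make no superiority claim from them.
4. Replace the stated 80% power with that of the randomised B versus C contrast, using the sponsor's expected p and q.

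Stratifying the pooled test by entry point is no substitute: the first-visit stratum has no C patients and contributes nothing, and each randomised contrast already lies within one stratum.

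This needs changes to the plan's wording and no new patients. The price is a much less favourable stated power and a primary aim that the present size may not answer.

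Alternatively, since recruitment is planned to December 2027, the sponsor may amend the allocation for future patients so that surgical candidates are randomised among all three groups, as the abstract states. That replaces the two-stage scheme, removes the late-entry randomisation and needs a protocol and consent amendment. It is an option, not the required correction.

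### The 0.66/0.34 split behind the 35 events, 57 subjects and 80% power is not fixed by the allocation scheme, and the contrast it powers is not a randomised one

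*Protocol article*

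**What the plan says.** The Sample size justification treats the trial as a two-group survival comparison. It takes "a proportion of subjects in Group 1 (upfront and deferred CN) of 0.66" and "a proportion in Group 0 (ICIs only) of 0.34", a relative hazard of 0.37 and a two-tailed alpha of 0.05, and concludes: "The calculated number of events needed to achieve 80% power was 35". A control median of 1.3 years, a censoring rate of 0.1 and 5 years of follow-up then lead to 57 subjects.

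The Methods paragraph of the abstract describes one allocation: patients "will be randomly allocated to three groups (1, upfront CN; 2, deferred CN; and 3, systemic therapy [ST] only".

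The Study timeline section describes something different:

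- **Eligible at the first visit:** "If they are eligible for surgery at the first visit, they will be randomly allocated to the upfront CN Group A" or to group B. Group C is not open to them.
- **Not eligible at first, eligible after induction:** randomised between B and ICIs only.
- **Never eligible:** continue on ICI therapy as group C, without randomisation.

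The ratio is stated once: "Patients will be randomly allocated in a 1:1 ratio". The article gives no expected share of patients for any route and no target or cap for any group.

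**The concern.** Required events and power depend directly on the split between the compared groups. A share of 0.66/0.34 is what equal allocation to three groups would give. Under the two-step scheme the split depends on how many patients are surgical candidates and when, so the protocol does not control it.

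There is also a question of what is being powered. The Study design section presents a randomised superiority trial of upfront or deferred CN against ICIs alone. If first-visit candidates cannot reach C, and C also takes patients who never become fit for surgery, then pooled A+B versus C compares patients who differ in surgical eligibility. A survival difference in favour of CN could then reflect selection, whatever its p-value.

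**Working it through.** **Inputs from the Sample size justification.** Two-sided alpha 0.05, power 80%, hazard ratio 0.37, shares 0.66/0.34, control median 1.3 years (rate ln 2/1.3 = 0.533 per year), censoring 0.1 per year, follow-up 5 years, N = 57.

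**1. Reproduce the plan's figures.**

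Events (Schoenfeld): (1.96 + 0.8416)² / (0.66 × 0.34 × (ln 0.37)²) = 7.849 / (0.2244 × 0.9885) = 35.4, stated as 35.

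Probability of an observed death: λ/(λ+0.1) × (1 − exp(−5(λ+0.1))). This is 0.807 for ICIs only (λ = 0.533) and 0.514 for CN (λ = 0.37 × 0.533). The weighted mean is 0.34 × 0.807 + 0.66 × 0.514 = 0.613, and 35/0.613 = 57.1, stated as 57.

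Both figures reproduce, given the 0.66/0.34 split.

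**2. Split implied by the Study timeline.** Let p be the share eligible at the first visit and q the share of the rest eligible after induction. Both are assumptions, because the article gives neither.

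- A = p/2
- B = p/2 + (1−p)q/2
- C = (1−p)(1−q/2)

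C equals 0.34 only along a line of (p, q) pairs, from p = 0.32 with q = 1 to p = 0.66 with q = 0; for example p = 0.5 with q = 0.64.

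**3. Power of A+B versus C at N = 57.** With C's share c, expected events are D = 57 × (0.807c + 0.514(1−c)), and power is Φ(√(D·c(1−c)) × 0.994 − 1.96), where 0.994 = |ln 0.37|.

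| C share | Power at N = 57 | Power at exactly 35 events |
|---|---|---|
| 0.15 | 52% | 56% |
| 0.20 | 62% | 65% |
| 0.25 | 70% | 72% |
| 0.34 | 79.5% | 80% |
| 0.50 | 86% | 84% |
| 0.75 | 79.5% | 72% |

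Events needed for 80% power are 42, 50 and 62 at C shares of 0.25, 0.20 and 0.15.

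Some assumed case mixes:

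- p = 0.2, q = 0.5: C = 0.60, power 86%
- p = q = 0.5: C = 0.375, power 82%
- p = 0.7, q = 0.5: C = 0.225, power 66%
- p = 0.8, q = 0.5: C = 0.15, power 52%

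**4. What is randomised.** A versus C: nobody. B versus C: only the second step, 57(1−p)q patients. The calculation assumes that hazard ratio 0.37 also applies there, with a 1:1 split and mean event probability (0.807 + 0.514)/2 = 0.66.

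| p, q | Randomised B:C | Power | Unrandomised in C, 57(1−p)(1−q) |
|---|---|---|---|
| 0.5, 0.5 | about 14 | 33% | about 14 |
| 0.5, 0.64 | about 18 | 41% | about 10 |
| 0.32, 1 | about 39 | 71% | 0 |

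The last two rows both have the assumed 0.66/0.34 split. Even there, the randomised comparison of surgery with no surgery has less than 80% power.

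**The case against.** The arithmetic in the Sample size justification is correct on its own inputs, and 0.66/0.34 can arise under the two-step scheme. A reader might infer that the scheme cannot produce that split, or that the trial is underpowered. The documents support neither inference. At N = 57, power is about 80% or better for any C share from about 0.34 to about 0.75, and p = q = 0.5 gives 82%, slightly above the stated figure.

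The unfavourable cases need a high p, and nothing in the article supports 0.7 or 0.8. Entry requires a Karnofsky score of at least 70, whereas CN candidates need at least 80, fewer than three IMDC features and a removable primary tumour. Non-candidates are therefore admitted by design. If p is 0.32 or lower, C is at least 0.34 whatever q is.

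Nor is it certain that 0.66/0.34 was meant as equal three-way allocation. The section cites real-world data in the same three groups, so the shares could be an expected case mix. The article does not say.

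All of this stands and limits the claim to a split that is not fixed. It does not rescue the 80%, which still rests on an input that the allocation neither sets nor supports with stated eligibility rates. It also leaves untouched the lack of randomisation between A and C.

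**Conclusion.** The concern holds in this form: the stated 80% power is not a property of the described design. It is too high at N = 57 if C falls below about 0.34 or rises above about 0.75, and roughly right or conservative in between. If the analysis is instead taken at exactly 35 events, the range with about 80% or more is narrower, with CN shares of roughly 0.35 to 0.65.

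The heavier consequence concerns the contrast itself. As long as A contains patients, or any never-eligible patient enters C, pooled A+B versus C is not a randomised comparison, and no value of the split repairs that. The randomised evidence on surgery versus no surgery comes from B versus C at the second step, with 33% to 71% power in the cases shown.

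These sizes rest on assumed p and q, on exponential survival and censoring with the plan's rates, and on hazard ratio 0.37 applying to B versus C as well.

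**What to change.** Reconcile the abstract, the Study timeline and the Sample size justification so that they describe one allocation. If the two-step scheme stands:

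- State the centres' expected p and q and the group shares they imply.
- Give events and power for A+B versus C as a range over plausible C shares, above as well as below 0.34.
- Say plainly that A+B versus C is not a randomised comparison.
- State separately the expected size and power of the randomised B versus C comparison.

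If one three-group randomisation is meant, the Study timeline must be reconciled with it. Equal three-way allocation gives 0.66/0.34 only if patients ineligible at the first visit are kept out of the powered comparison. If they still feed B and C as now described, C becomes p/3 + (1−p)(1−q/2): 0.54 at p = q = 0.5, 0.46 at p = 0.7, q = 0.5, and 0.42 at p = 0.8, q = 0.5. Which patients may be allocated to which treatment is for the investigators to settle.

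The cost is a recalculation and rewording of the sample size section, and the stated power may become less favourable. Changing the allocation would need a protocol amendment. If only first-visit candidates then counted towards the 57, more patients might have to be recruited.

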**Fig. 1 Fig1:**
[figure not shown]
Study flowchart. CN, cytoreductive nephrectomy; IMDC, International mRCC Database Consortium; Ipi, ipilimumab; mRCC, metastatic renal cell carcinoma; Nivo, nivolumab; KPS, Karnofsky performance status

Candidates for CN are patients with good performance status (Karnofsky performance status ≥ 80%) and less than three IMDC risk features and whose primary tumor could be surgically removed. Metastasectomy can be performed when the metastatic sites can be surgically removed. All patients eligible for ICI therapy will receive four cycles of intravenous nivolumab (3 mg/kg) plus ipilimumab (1 mg/kg) every 3 weeks as the induction phase, followed by a response evaluation. After the induction phase, intravenous nivolumab (3 mg/kg) will be administered 6 times every 2 weeks as the maintenance phase, followed by response evaluation. Nivolumab monotherapy will be maintained for a maximum of 2 years for those without adverse side effects. During ICI therapy, adverse events will be evaluated once per cycle. Patients will discontinue ICI therapy when they develop serious adverse events, including grade 3 or worse, according to the Common Terminology Criteria for Adverse Events version 5.0 (CTCAE v 5.0). In the upfront CN group, the induction phase will be within 6 weeks of surgery, whereas in the deferred CN group, surgery will be performed within 6 weeks of the induction phase. The study will be conducted over a period of 5 years.

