## Methods and analysis

### Study design

The current study is a prospective, randomized, open-label, multicenter, interventional, superiority clinical trial with a parallel-arm design, and will be conducted at the Yonsei University Health System (YUHS), which includes Severance Hospital, Gangnam Severance Hospital, and Yonsei Severance Hospital. After the startup phase, we will expand the study to other South Korean centers. The study was registered at ClinicalTrials.gov (NCT05753839). This trial complied with Standard Protocol Items: Recommendations for Interventional Trials (SPIRIT) guidelines. The SPIRIT checklist can be found in Additional file 1. All data will be anonymized and collected on structured case reporting forms.

This study will investigate whether upfront or deferred CN improves oncological outcomes (OS and PFS) in patients with synchronous mRCC and ≤ 3 International mRCC Database Consortium (IMDC) risk features compared to immune checkpoint inhibitors (nivolumab plus ipilimumab combination) alone.

To understand the role of CN in immuno-oncology, we will collect and analyze clinical data and samples (tumor tissue, blood, urine, and stool samples).

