#### Inclusion criteria

Core needle biopsy-proven metastatic renal cell carcinoma—only clear cell histologic subtypes are acceptable.Synchronous metastatic renal cell carcinoma with a primary tumor in the kidney.The patient must be willing to provide their human-derived materials.Age ≥ 19 years.Signed written informed consent must be obtained from all patients prior to any study-specific procedures.The patient must be willing and able to comply with the protocol.Measurable disease as per response evaluation criteria for solid tumors (RECIST) v 1.1.Life expectancy of greater than 4 months.Patients with more than one prognostic factor by the IMDC criteria (intermediate- or poor-risk group).Patients indicated nivolumab/ipilimumab, according to the recommendations by the national health authorities. The prescription of nivolumab/ipilimumab under the circumstances of the study is considered standard treatment.Karnofsky Performance status ≥ 70.Females with a negative serum pregnancy test unless childbearing potential can be otherwise excluded (postmenopausal, hysterectomy, or oophorectomy) and not lactating.Fertile women of childbearing potential (< 2 years after last menstruation) and men must use effective means of contraception (oral contraceptives, intrauterine contraceptive device, barrier method of contraception in conjunction with spermicidal jelly or surgical sterilization).The required laboratory values are as follows:Adequate bone marrow function (Absolute neutrophil count > 1500/mm3, platelets > 100 × 103/µl, hemoglobin > 10.0 g/dL)International normalized ratio (INR) ≤ 1.2 × upper limit of normal (ULN)Adequate hepatic function (bilirubin ≤ 1.5 × ULN, ALAT ≤ 2.5 × ULN)Adequate kidney function (eGFR > 35 mL/min)

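### A patient with exactly three IMDC features is in the population said to be randomised but cannot be a CN candidate, and may enter Group C unrandomised

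*Protocol article*

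**What the plan says.** The abstract (Methods) states: "Synchronous mRCC patients with ≤ 3 IMDC risk features will be randomly allocated to three groups". Study design puts the question of upfront or deferred CN against checkpoint inhibitors alone in "patients with synchronous mRCC and ≤ 3 International mRCC Database Consortium (IMDC) risk features". The inclusion criteria carry no upper IMDC limit.

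The text under Fig. 1 defines a CN candidate by three conditions: KPS of at least 80, "less than three IMDC risk features and whose primary tumor could be surgically removed".

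Study timeline ties randomisation to surgical eligibility. At the first visit: "If they are eligible for surgery at the first visit, they will be randomly allocated to the upfront CN Group A" or to the deferred group. A patient not eligible then starts checkpoint inhibitor induction and is reassessed. One who has become eligible is randomised to deferred CN or inhibitors only. For the remainder: "If not, they will continue with ICI therapy (maintenance phase) (Group C".

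Sample size justification powers OS for the two CN groups together against inhibitors only, with "a proportion of subjects in Group 1 (upfront and deferred CN) of 0.66 and a proportion in Group 0 (ICIs only) of 0.34".

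**The concern.** The two limits disagree at one value, three features, and that value decides whether a patient can be randomised. The abstract promises such a patient allocation among three groups, two of them surgical. The candidacy rule bars surgery, and the timeline then places the patient in the comparator if nothing changes during induction.

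Two things are at stake. First, Group C would hold some patients placed there because of a prognostic count and not by chance, while no patient would be placed in a CN group on that ground. If three features carry a worse prognosis than fewer, the OS comparison is tilted towards CN. Second, a reader of the results could not tell to which IMDC counts a conclusion on CN applies: up to three, as the abstract and Study design say, or up to two, as the candidacy rule implies.

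**Working it through.** **The limits side by side, for a patient with exactly three features**

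| Place | Limit | Three features? |
|---|---|---|
| Abstract, Methods (who is randomised) | three or fewer | inside |
| Study design (population of the CN question) | three or fewer | inside |
| Inclusion criteria | no upper limit | inside |
| Text under Fig. 1 (CN candidate) | fewer than three | outside |

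Following Study timeline: not a candidate at the first visit, so no randomisation between A and B; induction; reassessment. If the count is now below three and the other conditions hold, randomisation is between B and inhibitors only. Otherwise the patient continues in Group C with no randomisation. Allocation to A is not possible on either branch.

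**The plan's own figures**

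Inputs from Sample size justification: hazard ratio 0.37, two-sided alpha 0.05, power 80%, shares 0.66 and 0.34, control event rate 0.53 per year, censoring rate 0.1 (taken as per year), follow-up 5 years.

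- Events = (1.960 + 0.842)² / (0.66 × 0.34 × (ln 0.37)²) = 7.849 / (0.2244 × 0.9885) = 35.4. The plan states 35.
- P(event) = h/(h + 0.1) × (1 − exp(−5(h + 0.1))). With h = 0.53 this is 0.805; with h = 0.37 × 0.53 it is 0.512. Weighted: 0.66 × 0.512 + 0.34 × 0.805 = 0.611.
- N = 35 / 0.611 = 57.2, about 38 CN and 19 inhibitors only. The plan states 57.

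The plan's figures are reproduced.

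**Sensitivity of the OS comparison**

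The document gives neither the number of three-feature patients nor their hazard, so both are assumed. Suppose CN has no effect, and m of the 19 Group C patients are there solely because of three features, with k times the hazard of everyone else. The base hazard is set so that the Group C median is 1.3 years, with censoring 0.1 per year, 5 years of follow-up, and OS counted from entry for all. The apparent hazard ratio (CN against inhibitors only) solves the large-sample Cox score equation. The last column is the share of simulated trials (20,000 per cell) with a log-rank result favouring CN at two-sided 0.05.

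| m | k = 1.5 | k = 2 | k = 3 | False results for CN |
|---|---|---|---|---|
| 0 | 1.00 | 1.00 | 1.00 | about 3% |
| 1 | 0.98 | 0.97 | 0.96 | about 4% |
| 2 | 0.96 | 0.94 | 0.92 | 4-6% |
| 4 | 0.92 | 0.88 | 0.84 | 5-9% |

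**Power if such patients are left out and not replaced**

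All of them come from Group C, so each removes 0.805 expected events. CN stays at 38. With d events and CN share a, power = Φ(√(d·a·(1 − a)) × |ln 0.37| − 1.960), where |ln 0.37| = 0.994.

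- None out: d = 35, a = 38/57 = 0.667; √(35 × 0.2222) × 0.994 = 2.773; power 79%.
- Two out: d = 35 − 2 × 0.805 = 33.4, a = 38/55 = 0.691; √(33.4 × 0.2136) × 0.994 = 2.655; power 76%.
- Four out: d = 35 − 4 × 0.805 = 31.8, a = 38/53 = 0.717; √(31.8 × 0.2029) × 0.994 = 2.525; power 71%.

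**The case against.** The best defence is that entry may be wider than surgical candidacy, and that Study timeline together with the text under Fig. 1 is the operative rule. A site can follow it: not a candidate, so start induction and reassess. Only the abstract, in one condensed sentence, says that all patients up to three features are randomised; Study design names the population but does not say so. The flowchart is not shown and may indicate which limit applies.

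Much of this stands. A wider entry range is not in itself an error, and the document does not leave sites without a rule. What remains is that a stated rule on who is randomised conflicts with the stated rule on who can have surgery. A figure could not make the two written limits agree.

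A second defence is that unrandomised entry to Group C comes from the timeline and applies to every patient ineligible for surgery. That is correct. A reader might infer that the IMDC mismatch is the source of bias in the OS comparison, or that one common limit would remove it. The document supports neither: patients with KPS 70-79 meet the inclusion criteria but not the candidacy rule, and an unresectable primary leads the same way. Nor does it support the reading that three-feature patients are never randomised, since reassessment after induction may make some of them eligible.

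A third defence is adjustment. Baseline IMDC features and KPS are collected (Table 1) and multivariate Cox models are planned. These can reduce an imbalance. But if no three-feature patient is in a CN group, the model must extrapolate at that level, and it does not restore randomisation.

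**Conclusion.** The point holds in limited form. The limits conflict at exactly three features, and the consequence follows from the text: no randomisation at the first visit and, for those still ineligible after induction, unrandomised entry to the comparator of the powered OS analysis.

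The size due to this mismatch alone cannot be derived from the document. On the assumed inputs it is small for one or two patients (apparent hazard ratio 0.92 to 0.98) and noticeable only if several enter (0.84 to 0.92 for four). The tilt towards CN assumes that three-feature patients have the worse prognosis and that OS is counted from entry in all groups; the text shown does not state the starting point. It would be too strong to say that the mismatch invalidates the primary comparison. It should be corrected because it governs who is randomised and to whom the result applies, and because the correction is cheap.

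**What to change.** 1. Choose one upper IMDC limit, either fewer than three or three or fewer, as the clinical investigators judge right. Use it for both randomisation and CN candidacy in the abstract, Study design, the inclusion criteria and the text under Fig. 1.
2. Keep patients above that limit, who are never randomised, out of the randomised OS comparison and report them descriptively. Limit the conclusion on CN to the IMDC counts actually randomised.

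The cost is mainly a wording amendment; recruitment is planned to December 2027, so a single rule can still be applied. With the lower limit the population is slightly narrower. If patients above the limit had been counted towards the 57, either replace them or restate the share and the power in Sample size justification (about 76% with two left out, 71% with four). This does not close the same route for KPS 70-79 or an unresectable primary, which needs its own correction in Study timeline.
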